**Methods:**

The primary aim of this study is to test the feasibility of an educational intervention to advance clinicians’ application of gait analysis in CYPwCP, to inform a definitive trial. The secondary aim is to measure the effect that appropriate IGA training has on physiotherapists’ knowledge, skills, confidence and behaviours. This will be a two-arm feasibility randomised controlled trial with an experimental and control group. The 6-week on-line intervention uses a multicomponent approach grounded in behavioural change techniques. A repeated measures design will be adopted, whereby participants will complete outcome measures at baseline, immediately after the intervention and at 4 months. The primary outcome measures (trial feasibility-related outcomes) are recruitment and engagement. The secondary outcome measures (trial research-related outcomes) are knowledge, skills, confidence and practice change. Outcome measures will be collected via online questionnaires and during observed skill assessments. Analysis of data will use descriptive statistics, two-way mixed ANOVA model and qualitative content analysis.

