***Secondary***			
Knowledge	EG will have improved knowledge scores relative to CG EG will increase knowledge scores EG will maintain knowledge scores	MCQ test	Effect sizes and 95% CIs from repeated measures ANOVA test and Kruskal–Wallis *H*-test
Skills	EG will have improved practical skills scores relative to CG EG will increase practical skills scores EG will maintain practical skills scores	OSCE	Effect sizes and 95% CIs from repeated measures ANOVA test and Kruskal–Wallis *H*-test
Attitudes	EG will have improved gait-related practice behaviours	Questionnaires: Self-reported knowledge and confidence, practice change, practice change planning, beliefs, semi-structured interviews	Effect sizes and 95% CIs from repeated measures ANOVA test Framework method for qualitative data (Ritchie 2014)
Satisfaction	EG will demonstrate a high satisfaction rate	Satisfaction questionnaire	Descriptive statistics

*EG* experimental group, *CG* control group, *VLE* virtual learning environment, *MCQ* multiple-choice question, *OSCE* observed standardised clinical examination

Recruitment will be determined as feasible if study is able to recruit 24 participants within 4 months [22, 23]. Retention rates will be considered at two stages: (1) from expression of interest to consent — it will be deemed feasible if greater than 50%, and (2) from consent to course completion — it will be deemed feasible if greater than 75% [24, 25]. Additionally, engagement (participants’ interactions with an online system) data will be collected during intervention via the analytics tools in the QMUL Virtual Learning Environment which log the detail of activity access, time, and completion for each component. These analytic tools are part of the general-purpose dashboard and provide an algorithmic representation of student online behaviours based on whether the behaviour occurred and for how long, rather than quality of these behaviours. Previous studies show that these analytics have been positively correlated with student performance [26–28]. It will be deemed feasible if the average proportion of completed learning sessions and tasks will be ≥ 66%.

Secondary outcomes are as follows: knowledge, skills, attitudes, and satisfaction will be collected via online questionnaires (SurveyMonkey) and during skill tests (OSCE). Knowledge, skills, and attitudes will be collected at three timepoints (Table 1).

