##### Re-test (4-month post-intervention)

Questionnaire attitudes (planning practice change, implemented practice change, beliefs), confidence (self-rated), and knowledge (self-rated and multiple-choice question test)OSCE of a different patient case (scored against the same criteria as at baseline)

Knowledge and skills retention as well as attitudes will be measured between timepoints, with a focus on changes between baseline and immediately post intervention and at 4-month follow-up. Satisfaction questionnaire will contain 28 items, each assessed on a 5-point Likert scale, related to the relevance and scientific quality of the content, the educational structure, and delivery. Satisfaction feedback will be collected immediately after intervention delivery (experimental group).

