#### Data management and research governance

A baseline table (descriptive statistics and frequencies) will compare the demographic and clinical characteristics including gender, age, experience, education, practice setting, contract type, study leave availability to participate in intervention, access to equipment, and gait analysis training. The primary outcomes will be reported using descriptive statistics. The quantitative variables will be presented as means and standard deviations.

A preliminary analysis of between-group differences will be conducted to determine the range of potential effect sizes from repeated measures ANOVA. Feasibility outcomes will be presented as number of participants meeting the a priori definitions. Kendall’s tau-b (*τ*_b_) correlation coefficient will be used to measure of the strength and direction of association that exists between two variables measured on at least an ordinal scale. To explore the extent and patterns of missing outcome data, we will report the proportion of missing values per item and the proportion of participants who will complete all items on the questionnaires. The proportion of missing data will also be reported for the other key outcomes and compared between the participants from intervention and control groups.

Qualitative data will be analysed according to the framework approach [30], a realist approach located within an interpretivist frame. The opinions and experiences of participants will be explored to understand any barriers and facilitators related to running of the educational intervention. During active familiarisation, the textual data will be coded, and codes will be organised into themes and subthemes to construct a thematic framework to aid indexing. To ensure rigour and consistency, the analysis process will undergo investigator triangulation. In this process, different observers, examiners, and analysts will compare and check data collection and/or interpretation [30, 31]. Qualitative data will be presented as quotes and descriptive summaries.

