One of the main challenges will be associated with possible low uptake in the study and high drop-out rate. High work pressures and limited time to study may result in reduced opportunity or willingness to participate in the intervention and multiple assessments.

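### The planned repeated measures ANOVA drops anyone missing one of three assessments and leaves baseline unadjusted, so group-difference intervals are wider than they need be

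*Protocol article*

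**What the plan says.** The protocol article names the analysis of the secondary outcomes in three places.

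- Table 3 (Secondary) gives "Effect sizes and 95% CIs from repeated measures ANOVA test and Kruskal–Wallis *H*-test" for knowledge (MCQ test) and skills (OSCE), and "Effect sizes and 95% CIs from repeated measures ANOVA test" without the rank test for attitudes, a row that includes self-rated knowledge and confidence.
- The Abstract (Methods) states: "Analysis of data will use descriptive statistics, two-way mixed ANOVA model and qualitative content analysis".
- Data management and research governance takes the range of potential between-group effect sizes from the repeated measures ANOVA.

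These outcomes are measured at baseline, immediately after the 6-week course and 4 months later. The Re-test section describes the comparison between timepoints "with a focus on changes between baseline and immediately post intervention and at 4-month follow-up". No baseline covariate is named.

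On missing scores, Data management and research governance says "To explore the extent and patterns of missing outcome data, we will report the proportion of missing values per item", and adds a comparison of missingness between arms. Process evaluation and implementation outcomes adds an analysis of withdrawals. The Discussion warns: "One of the main challenges will be associated with possible low uptake in the study and high drop-out rate".

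Study aims and objectives includes setting the sample size of a definitive trial, and the process evaluation will review the anticipated effect size for that trial. Data collection, management, and analysis names SPSS, rules out a power analysis and calls all analyses exploratory.

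**The concern.** A classical two-way mixed ANOVA with three time levels has two properties that matter here.

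First, it needs a complete row for each participant. Someone who sits the post-intervention MCQ and OSCE but misses the 4-month assessment is removed from the post-intervention comparison too, although that score was observed.

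Second, with baseline as one of the time levels, the group-by-time contrast between baseline and a follow-up is a difference in mean change. That is a valid comparison under randomisation, but it is less precise than one that adjusts for baseline unless the correlation between assessments is very high.

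With a minimum of 12 per arm there is little information to spare, and the effect sizes have a stated later use. Intervals that are needlessly wide weaken that use. In addition, if completers differ from non-completers, the completer-only estimate describes a selected group.

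**Working it through.** **Inputs from the protocol article.** At least 12 per arm, so 2 × 12 = 24 (Sample size). Three timepoints. There is no SD, effect size, power or correlation, so the plan has no power figure to reproduce.

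**Assumptions.** Equal variance at each visit and a common correlation ρ between visits, shown over a range because the protocol gives no value. No clustering by trust.

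**Step 1: baseline adjustment with complete data.** In units of the outcome variance:

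- change-score contrast: 2(1 − ρ)
- baseline-adjusted contrast, large sample: 1 − ρ²
- ratio: (1 − ρ²) / [2(1 − ρ)] = (1 + ρ)/2

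At N = 24 the adjusted variance is multiplied by (N − 3)/(N − 4) = 21/20 = 1.05, for chance baseline imbalance. The t quantile uses 21 degrees of freedom instead of 22.

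| ρ | Large-sample variance ratio | Variance ratio, N = 24 | CI width ratio, N = 24 | Change in CI width |
|---|---|---|---|---|
| 0.3 | 0.65 | 0.683 | 0.828 | 17% narrower |
| 0.5 | 0.75 | 0.787 | 0.890 | 11% narrower |
| 0.7 | 0.85 | 0.892 | 0.947 | 5% narrower |
| 0.8 | 0.90 | 0.945 | 0.975 | 2.5% narrower |
| 0.9 | 0.95 | 0.997 | 1.002 | none |

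**Step 2: loss at 4 months only.** Assume 6 of 24 (3 per arm) miss only the last visit, completely at random. The ANOVA then uses 18 people at every timepoint, while a mixed model keeps all 24 post-intervention scores. A simulation of 20,000 runs per scenario compared completer-only ANOVA contrasts with a baseline-adjusted, unstructured repeated-measures model fitted by maximum likelihood.

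| ρ | Variance ratio, post-intervention | Variance ratio, 4 months |
|---|---|---|
| 0.3 | 0.51 | 0.70 |
| 0.5 | 0.60 | 0.80 |
| 0.7 | 0.69 | 0.90 |
| 0.8 | 0.71 | 0.92 |

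At ρ = 0.5 the SD of the post-intervention difference is 0.469 for the ANOVA and 0.362 for the mixed model, in SD units of the outcome; (0.362/0.469)² = 0.60. With no loss the two SDs are 0.408 and 0.362.

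Hand check: the post-intervention ratio should be near (18/24) × the N = 24 ratio of Step 1. For ρ = 0.3, 0.5 and 0.7 this gives 0.75 × 0.683 = 0.51, 0.75 × 0.787 = 0.59 and 0.75 × 0.892 = 0.67, close to the simulated values.

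**Step 3: how fast complete cases erode.** If each of the three assessments were missed independently (an assumption), the expected number of complete cases is 24q³ for per-visit completion q. This is 20.6 at 95%, 17.5 at 90%, 14.7 at 85% and 12.3 at 80%.

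**The case against.** **The analyses are secondary and exploratory, and an unseen analysis plan may settle covariates and missing data.** In part this stands. The feasibility criteria are descriptive and do not depend on the ANOVA, so a reader who infers that the go/no-go decision is at risk goes too far. But the protocol does not leave the method open: it names it three times. Listwise deletion and change-score contrasts are properties of that method. Baseline as a time level is inferred rather than stated, but it is the natural reading of a group-by-time ANOVA on these three timepoints.

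**No group difference with an interval at 4 months?** A reader might infer that the plan yields only an omnibus interaction test. The documents do not support this. Table 3 promises effect sizes with 95% CIs, and contrasts can be taken from an ANOVA.

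**Only 18 complete cases?** A reader might take the 75% retention threshold (0.75 × 24 = 18) as the expected number. That threshold is a feasibility criterion running from consent to course completion. It is neither a forecast nor a 4-month figure. People lost before the end of the course will often have no follow-up score, and a mixed model cannot recover them. The gain in Step 2 therefore depends on loss falling after the post-intervention assessment.

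**Bias.** A reader might infer that the ANOVA estimate will be biased and the mixed model will not. Neither follows. The documents do not say how drop-out relates to scores, and the mixed model rests on missing at random, which the data cannot verify. The planned description of missingness and withdrawals is useful, but does not return discarded scores to the estimate.

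**High correlation removes the gain.** This is true near 0.9 with complete data. For the OSCE such a value is unlikely, because a different patient case is used each time.

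**Some hypotheses need change from baseline.** Table 3 also expects the experimental group to increase and maintain its scores. A model with baseline only as a covariate does not directly address those, so the within-group analysis must stay.

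**Conclusion.** The point holds for the MCQ, the OSCE, self-rated confidence and self-rated knowledge, all measured at baseline. The baseline argument does not reach practice change, which Table 1 schedules only after the intervention and at 4 months.

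The loss is mainly one of precision. Under the assumed correlations it is modest with complete data, and larger for the post-intervention comparison if people miss only the last visit. It threatens no confirmatory conclusion. It does affect the effect sizes and intervals carried to the definitive trial, and it can be avoided with data already being collected. The change should be made.

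The figures rest on equal variances, a common correlation, drop-out completely at random and no trust effect. None of these can be checked from the protocol article.

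**What to change.** For the between-group comparisons on these four outcomes, replace the ANOVA with a linear mixed model:

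- Outcomes: post-intervention and 4-month scores, using every available score.
- Fixed effects: baseline score, group, time and group-by-time, with baseline-by-time if wanted.
- Within-participant correlation: unstructured residual covariance or a participant random intercept. Without one of these, two scores from one person are treated as independent and the post-intervention score does not properly inform a missing 4-month score.
- Trust: add a random intercept if it is estimable, because participants from one healthcare trust are allocated together. State what unit a private practitioner belongs to.
- Estimation: REML with Kenward–Roger or Satterthwaite degrees of freedom.
- Reporting: adjusted group difference with 95% CI at each timepoint, labelled exploratory, with the missing-at-random assumption stated.

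Keep the ANOVA, or within-group change from baseline with its CI, for the hypotheses that the experimental group increases and maintains its scores. Align the Abstract, Table 3 and Data management and research governance.

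The cost is analysis wording only: no new data, and the named software can still be used.

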### Study aims and objectives

The primary aim of this study is to determine the feasibility of an educational intervention to advance clinicians’ application of instrumented gait analysis in children and young people with cerebral palsy, to inform the design of a full trial. Objectives are as follows:

To establish the feasibility of a future randomised controlled trial of educational intervention.Assess the rate of participant enrolment, retention and compliance with intervention.Assess whether the inclusion and exclusion criteria for participants are appropriate.Assess whether the duration of intervention is appropriate.Assess whether intervention delivery in a virtual learning environment is feasible and acceptable.Explore if the outcome measures are appropriate for the study aims.Define the sample size for a definitive trial.Explore the fidelity of intervention delivery.Further understand the barriers and facilitators of the intervention.

The secondary aim is to measure the effect that appropriate IGA training and its delivery has on physiotherapists’ knowledge, skills and attitudes.

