### Trial design

This will be a two-arm feasibility randomised controlled trial with an experimental and control group. The 6-week on-line intervention delivered as part of the trial is a stand-alone, post-graduate level educational course called Virtual Gait Analysis Course for Paediatric Physiotherapists (VGAPP). Eligible physiotherapists who consent to take part in the study will be randomly allocated into experimental and control groups. A repeated measures design will be adopted, whereby participants will complete outcome measures at baseline, immediately after the intervention, and at 4 months. This will include collection of feedback as part of a full process evaluation.

The trial will be determined feasible if a priori set criteria based on primary outcome measures and included in the process evaluation will be achieved at or above agreed levels (see the ‘Outcome measures’ section of ‘Methods’). After conducting and reviewing outcomes of the full evaluation process, the decision about delivery of the definitive trial will be made.

Figure 1 shows the study flow diagram, and Table 1 indicates the schedule of enrolment, intervention, and outcome measures [18].

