***Primary***			
Recruitment	Study will recruit 24 participants	Number of participants	Descriptive statistics
Retention	Study will retain 75% of sample	Number of participants	Descriptive statistics
Engagement	The average proportion of completed VLE items will be ≥ 66%	Average proportion of completed VLE items	Descriptive statistics

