### Sample size

Considering the study objectives and recommendations, the target sample size will be of a minimum 12 participants per trial arm; therefore, a minimum of 24 in total is anticipated. Guidance from the National Institute for Health Research (NIHR) indicates that a sample size of 30 is appropriate to answer the questions posed by a feasibility trial [23]. A lower number of participants will be better suited for an educational intervention for clinicians — it will ensure delivery of a high-quality learning experience and allow for active engagement with tutors during problem-based learning within the experimental group. Furthermore, the stakeholder focus groups including of clinicians and educators reviewed the proposed sample size and reported it as appropriate for the feasibility trial.

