### Assignment of intervention

#### Allocation, concealment mechanism, and implementation

Participants who meet the inclusion criteria and return the consent form will be assigned an ID number in the Microsoft Excel spreadsheet. Participants will be assigned to groups randomly. In case there are more eligible physiotherapists than spaces, participants will be chosen by the number generation software which will be used in the allocation process. This will be conducted by an external person not related to the study or the research team. To avoid contamination, participants from the same healthcare trusts will be randomised to the same group.

Information about group randomisation will be provided in the participant’s information sheet. Participants in this study will not be blinded to the group allocation or deceived. This was discussed in the stakeholder focus groups who agreed that in the context of clinical practice, deceiving participants could mean a loss of their study/annual leave if pre-booked specifically to attend the intervention as well as potential cancelations of clinics in the control group. Participants will be informed about their allocation at the time of receiving instructions with the QMUL VLE platform access. At this time, the control group will be informed about timings of gaining their access to the full intervention and all resources provided to the experimental group after final assessments are completed. Participants will be informed that they are free to withdraw at any time without needing to provide a reason and with no penalties or detrimental effects.

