Baseline comparisons will be conducted to detect any substantial differences between participants recruited from the control and intervention arms. Sample size and anticipated effect size defined for the definitive trial will be reviewed and assessed for feasibility. Participant withdrawals and number of participants lost to follow-up (and where possible reasons and participants’ key baseline characteristics) will be analysed. The study protocol adherence will be reviewed within the research team. Fidelity to the trial protocol including follow-up, dosage of the intervention, crossover between study arms, and adherence to intervention delivery plan will be assessed against study protocol and participant timelines. Any changes to the protocol will be reported.

Furthermore, appropriateness of the trial design for the trial aim, inclusion and exclusion criteria, outcome measures, and intervention components will undergo an exploratory analysis of participants’ outcomes, engagement with content, and assessments, together with qualitative analysis of participants and educators’ feedback. Sustained participant interest throughout the trial period and sustained staffing levels to deliver and facilitate participants’ learning journey during intervention will be explored to inform the sustainability criteria for the definitive trial. The implementation cost analysis will be explored with the aim to inform the design of a full cost-utility analysis alongside a future definitive trial. Implementation cost will include the cost of administration involved in running the trial and cost related to production and delivery of the intervention and assessment components — such as speaker fees, and OSCE examiners and moderators will be reviewed.

In addition, the COM-B model and the behaviour change techniques taxonomy (BCTT) [35], widely used frameworks in behaviour change and implementation research, will support the process evaluation analysis and an in-depth exploration of the barriers and facilitators of implementing the feasibility trial.

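### The recruitment criterion tests whether the pilot fills its own 24 places in 4 months; no stated criterion links the observed rate to what the definitive trial would need

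*Protocol article*

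**What the plan says.** Among the objectives under Study aims and objectives is "To establish the feasibility of a future randomised controlled trial of educational intervention"; assessing the enrolment rate and defining the definitive sample size are also listed there.

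Table 3 gives the recruitment target as "Study will recruit 24 participants", measured as a number of participants. The text below it adds the time limit: "Recruitment will be determined as feasible if study is able to recruit 24 participants within 4 months".

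The figure of 24 comes from the Sample size section: "the target sample size will be of a minimum 12 participants per trial arm; therefore, a minimum of 24 in total is anticipated". Participant timeline also has 24 enrolled. Under Allocation, concealment mechanism, and implementation: "In case there are more eligible physiotherapists than spaces, participants will be chosen by the number generation software".

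On how the criteria are used, Trial design says "The trial will be determined feasible if a priori set criteria based on primary outcome measures and included in the process evaluation will be achieved", and that the decision on the definitive trial follows review of the full evaluation. The section on process evaluation and implementation outcomes lists recruitment rate, which it refers back to the thresholds in Methods, and coverage of the eligible population. It also says: "Sample size and anticipated effect size defined for the definitive trial will be reviewed and assessed for feasibility".

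**The concern.** A recruitment criterion in a feasibility trial should help to tell a definitive trial that can be recruited from one that cannot. This one compares the pilot's enrolment with the pilot's own target. Above the pass mark it carries no further information. Filling the places in two months (24/2 = 12 per month) or in four (24/4 = 6 per month) gives the same verdict. So does having 40 eligible volunteers for 24 places in four months (40/4 = 10 per month), because the surplus is removed by lot. Those 12 and 10 per month are hypothetical cases, but they are the evidence that would matter most for a larger trial.

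At stake is the meaning of a favourable recruitment verdict. The Discussion names recruitment as an uncertainty that the study should reduce, and low uptake as one of its main challenges. A pass could be reported when the rate behind it would supply a large trial only over many years.

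**Working it through.** **Inputs from the protocol article**
- Pilot size: 12 per arm (Sample size).
- Time limit: 4 months (text below Table 3).
- Retention: "Study will retain 75% of sample" (Table 3), used here as the proportion with evaluable outcomes.

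**Inputs assumed, because the article gives none**
- Two-sided alpha 0.05, power 80%, 1:1 allocation, comparison of two means.
- SMD 0.8, 0.5 or 0.3.

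**Step 1, the plan's own figure.** 2 × 12 = 24, which reproduces the recruitment target. The implied floor is 24/4 = 6.0 per month.

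**Step 2, illustrative definitive trial.** The number per arm is from the two-sample t-test; total recruited = 2 × (number per arm)/0.75, rounded up; months = total/6.

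| Assumed SMD | Per arm | Evaluable | Recruited at 75% retention | Months at 6 per month |
|---|---|---|---|---|
| 0.8 | 26 | 52 | 70 | 11.7 |
| 0.5 | 64 | 128 | 171 | 28.5 |
| 0.3 | 176 | 352 | 470 | 78.3 |

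**Step 3, cross-check.** The normal approximation gives totals of 67, 168 and 467, hence 11.2, 28.0 and 77.8 months. The choice of formula does not matter here.

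**Step 4, sensitivity (normal approximation).** At 90% power the totals are 88, 227 and 624, or 14.7, 37.8 and 104.0 months. The plan sends participants from the same healthcare trust to the same group; if the definitive trial did likewise, a design effect would apply. With an assumed design effect of 1.2 at 80% power, the totals are 81, 202 and 561, or 13.5, 33.7 and 93.5 months.

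**Step 5, precision of a bare pass.** If exactly 24 were observed in 4 months with no cap in play, the exact Poisson 95% CI for the count is 15.4 to 35.7, or 3.84 to 8.93 per month. For the SMD 0.5 case this gives 171/8.93 = 19 months to 171/3.84 = 44 months. The interval describes a count at the pass mark; it is not a forecast.

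**Step 6, what the rule returns.** In every row of Step 2 recruitment is judged feasible. The verdict cannot vary with the definitive sample size, because that quantity is not in the rule.

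**The case against.** The strongest reply is that this is one component and not the whole decision. Trial design puts the decision after the full evaluation, which is to consider recruitment rate, coverage and the definitive sample size. That stands. A reader might infer that the plan decides on the definitive trial without looking at its size; the documents do not support this. What remains is that the process evaluation takes its feasibility thresholds from Methods, and its review of the definitive sample size has no stated criterion.

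A reader might also infer that the primary outcome fails to answer the primary aim. That goes too far. Recruitment is one of three primary outcomes, a separate criterion covers conversion from expression of interest to consent (above 50%), and the aim also covers retention, delivery, outcome measures and fidelity.

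Nor is the rule free of any rate, since the time limit sets a floor of 6 per month. And the definitive sample size is an output of this study, so it cannot be fixed now. Both points stand, but neither prevents the sponsor from fixing a maximum recruitment period now and applying it to a range of sample sizes later.

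The durations are illustrative. The spread of about 1 to 6.5 years is the spread of the assumed SMDs, not a prediction. An analysis adjusted for baseline would lower the numbers by an amount that the document does not allow one to compute. The true rate could be well above the pass mark, and a definitive trial could recruit differently.

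Finally, one might argue that pilot participants, all of whom are to be offered the course, deplete the pool. The size of the eligible population is not given, so the effect of losing 24 cannot be judged, and the point here does not rely on it.

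**Conclusion.** The point holds for the recruitment criterion. It tests whether the pilot fills its own places, at a floor of 6 per month that is not derived from the definitive trial's needs, and demand above 24 does not enter it. The process evaluation gathers the relevant information, but no stated criterion joins the rate to the definitive sample size. The same favourable verdict would cover definitive trials of roughly 12, 28 or 78 months' recruitment, under the assumed SMDs, 80% power, two-sided 5% alpha, the plan's 75% retention and a constant 6 per month. The pilot's data are unaffected; the weakness is in what a recruitment pass can be taken to mean. The change is worth making because it is specific and cheap.

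**What to change.** Keep 24 in 4 months as the pilot's operational target. Then amend the recruitment text under Outcome measures and the matching text in the process evaluation section:

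1. Measure recruitment as the monthly rate of all eligible, consenting physiotherapists over the full window, including those not drawn by lot, with a 95% CI. If the call closes early because places are filled, use the time it was open as the denominator.
2. Project that rate and its limits onto a range of plausible definitive sample sizes. Base the range on a target effect size, not on the pilot's estimate, which will be imprecise with about 12 per arm. Include a design effect if same-trust allocation is to continue.
3. Judge recruitment feasible for the definitive trial by comparing the projected duration with a maximum recruitment period that the sponsor sets before the recruitment data are reviewed. The document offers no basis for a particular limit, so none is suggested here.

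The cost is wording and a dated screening and consent log; consent forms are already returned electronically. The recruitment verdict may become less favourable. The randomised comparison, its assessments and the number enrolled do not change.
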